#### Analyses: secondary outcomes

Secondary outcomes will be analysed as described above. The results will be presented as outlined in Tables 3 and 1 (components of the primary outcome).

**Table 3 Tab3:** Secondary outcomes

Outcome	Nasal HF group (*n =* XXX)	Control group (*n =* XXX)	Risk difference or difference of means or difference of medians (95% CI)
Time to desaturation—seconds^a^	Mean (SD) or median (IQR)	Mean (SD) or median (IQR)	
Duration of desaturation—seconds^a^	Mean (SD) or median (IQR)	Mean (SD) or median (IQR)	
Median SpO_2_^a^	Mean (SD) or median (IQR)	Mean (SD) or median (IQR)	
Bradycardia (HR < 100 bpm)^a^	XX (%)	XX (%)	
Time to bradycardia—seconds^a^	Mean (SD) or median (IQR)	Mean (SD) or median (IQR)	
Duration of bradycardia—seconds^a^	Mean (SD) or median (IQR)	Mean (SD) or median (IQR)	
Median HR^a^	Mean (SD) or median (IQR)	Mean (SD) or median (IQR)	
Number of intubation attempts	Mean (SD) or median (IQR)	Mean (SD) or median (IQR)	
Total duration of all intubation attempts (successful and unsuccessful)—seconds^c^	Mean (SD) or median (IQR)	Mean (SD) or median (IQR)	
CPR and/or adrenaline administration within 1 h of intubation attempt^b^	XX (%)	XX (%)	
Pneumothorax diagnosed within 72 h after randomisation^b^	XX (%)	XX (%)	
Any	XX (%)	XX (%)	
Requiring drainage with needle thoracocentesis or intercostal catheter	XX (%)	XX (%)	
Death within 72 h after randomisation^b^	XX (%)	XX (%)	

^a^During first intubation attempt

^b^Specified as serious adverse events in trial

^c^Sum of each separate intubation attempt

*IQR* interquartile range, *SpO*_*2*_ peripheral oxygen saturation, *HR* heart rate, *Bpm* beats per minute, *CPR* cardiopulmonary resuscitation

There will be no subgroup analyses performed for secondary outcomes.

### 28. Missing data

Every attempt will be undertaken to retrieve missing data. The primary outcome is recorded on a paper CRF by the investigator at the cot-side, to provide a backup to the video recording and time stamped downloadable oximetry recording. We therefore expect there to be very few instances in which the primary outcome cannot be determined and therefore do not anticipate needing to use multiple imputation to deal with missing data. Imputation will not be used for missing physiological data, for example in the event of loss of pulse oximetry signal or failure of video recording.

Multiple imputation or inverse probability case weights may be used to deal with missing data.

### 29. Additional analyses

Subsequent analyses that are not specified in the protocol may be performed if requested by journal editors or reviewers. These will be performed consistently with the principles of this analysis plan, as far as possible. Subsequent analyses of a more exploratory nature will not be bound by this strategy, but are expected to follow the broad principles described.

There will be graphical displays of results to present data.

Other additional analyses to be analysed and reported subsequent to the main trial include an additional sub-study will examine Near InfraRed Spectroscopy (NIRS) in a subset of babies undergoing randomisation in the trial. These data will be analysed separately and submitted for publication separately.

### 30. Harms

Incidence of the following serious adverse events will be compared between groups:
Incidence of pneumothorax within 72 h after randomisation, diagnosed by either transillumination of the chest and/or by chest X-rayIncidence of pneumothorax requiring drainage (via needle thoracocentesis or insertion of an intercostal catheter) within 72 h after randomisationIncidence of cardiac compressions and/or adrenaline administration within 1 h after the first intubation attemptDeath within 72 h after randomisation

These outcomes will be reported with 95% CI, without adjustment for multiplicity, given that type I error rates larger than 0.05 may be important. If journal editors or reviewers request it, *P* values may be reported for the comparisons of adverse events between treatment groups.

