### 10. Randomisation

Each intubation episode is randomly allocated in a 1:1 ratio to either nHF or control, stratified by:
Centre (Royal Women’s Hospital or Monash Newborn),Postmenstrual age (≤ 28 weeks' gestation; > 28 weeks' gestation)Use of premedication for intubation.

The randomisation sequence uses random permuted blocks with varying block sizes. To enable rapid randomisation following the decision to intubate by the clinical team, the randomisation is performed at the cot-side using a smartphone or computer with online access to the Research Electronic Data Capture (REDCap) [4] randomisation tool. Randomisation is web-based, using a password-protected, secure sockets layer (SSL)-encrypted website. The randomisation sequence was developed by an independent statistician at the Murdoch Children’s Research Institute, Melbourne, Australia. The group allocations are unblinded, due to the nature of the intervention. Intubation episodes, rather than infants, are randomised. An infant who has previously had an intubation episode randomised within the study can have subsequent intubation episodes randomised if (1) the premedication randomisation stratum differs between the studied intubations or (2) there is at least 1 week between the studied intubations for intubations where premedications are used.

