### 11. Sample size

The sample size of 246 intubation episodes is based on a previous study [5], which examined 206 neonatal intubations by junior medical staff. This study found a 29% successful intubation rate at the first attempt without peripheral oxygen desaturation > 20% or bradycardia < 100 beats per minute. With a power of 90% to detect an increase in the incidence of successful intubation without physiological instability from 30 to 50%, and two-sided alpha 0.05, at least 123 intubation episodes in each group (246 total) are required.

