### 19. Adherence and protocol deviations

### 20. Analysis population

The randomised population will comprise at least 246 intubation episodes, with infants randomised to either nHF or control. The analysis population will be created by removing the infants who met post-randomisation exclusion criteria from the randomised population, as outlined below.

On October 29, 2020, the Trial Steering Committee sought advice from the independent DSMB regarding post-randomisation exclusion criteria, with three deidentified randomisation episodes presented for discussion. These DSMB were blinded to trial data regarding the treatment arm and outcomes of the infants discussed.

Based on advice from the DSMB, the Trial Steering Committee reached consensus agreement regarding the following criteria for post-randomisation exclusions on 19 February 2021.
Randomised in error (patient was not intubated)Failure to meet inclusion criteriaMeeting exclusion criteria at the time of randomisation (e.g. bradycardia, abdominal wall defect)Parental withdrawal of consentParental consent declined in retrospective consent group

Therefore, the intention-to-treat (ITT) population will include all randomised infants and intubation episodes, regardless of exposure to the allocated treatment or adherence to the trial protocol, excluding the intubations which meet the post-randomisation exclusion criteria described above.

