#### Per-protocol analysis

We will undertake a per protocol analysis for the primary outcome if there are infants in the control group who received nHF or other apnoeic oxygenation during intubation or infants in the nHF group who never received the intervention. The following will not be deemed protocol violations: high flow prongs are placed and then dislodge or mechanical failure of machine.

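### Section 30 names no population for harms, and by default the plan leaves out serious adverse events in infants intubated under their allocation but later found ineligible

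*SAP article*

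**What the plan says.** Section 30 (Harms) lists four events: any pneumothorax, pneumothorax needing drainage, cardiac compressions and/or adrenaline, and death. It introduces them with "Incidence of the following serious adverse events will be compared between groups" and names no analysis set.

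Two statements in Section 4 could supply one, and they differ. Overall principles says that every randomised episode contributes its outcome data. Section 20 (Analysis population) says "The analysis population will be created by removing the infants who met post-randomisation exclusion criteria from the randomised population" and calls the result the intention-to-treat population.

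Section 20 gives five grounds for removal: "Randomised in error (patient was not intubated"), failure of an inclusion criterion, presence of an exclusion criterion at randomisation, withdrawal of consent, and refusal of retrospective consent.

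The only other set is per-protocol, and it is limited to one endpoint: "We will undertake a per protocol analysis for the primary outcome". No safety population is defined.

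The four harms also appear among the secondary outcomes in Section 26 and in Table 3. Secondary outcomes use the general methods of Section 27, with allocated group as the predictor.

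**The concern.** Removing ineligible episodes is an argument about efficacy: it keeps the treatment comparison to the infants the trial meant to study. It does not carry over to harms. An infant who underwent laryngoscopy under a randomised allocation was exposed to the trial procedure, whether or not a breach of eligibility came to light later. If that infant then had one of the listed events, it belongs in the trial's account of harm.

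The events are likely to be few, so a single omission could visibly change the harms table. The Introduction calls the technique untested in neonates. Section 30 declines multiplicity adjustment because it wants to remain sensitive to harm, and losing events from exposed infants works against that aim. If the set stays unnamed, the analyst must also choose between two conflicting statements after the data are in, in a trial that is not blinded.

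**Working it through.** **Step 1. Which set applies to harms?**

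| Place in the SAP | What it implies for harms |
|---|---|
| Section 4, Overall principles | All randomised episodes |
| Section 20 | Randomised episodes minus five kinds of exclusion |
| Per-protocol analysis | Not applicable (primary outcome only) |
| Section 26 | Harms are secondary outcomes |
| Section 27 and Analyses: secondary outcomes | General methods, by allocated group |
| Section 30 | No set named |

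Section 20 is the specific definition and Overall principles is a general statement. An analyst following the plan would most likely build Table 3 on the Section 20 set. That is the default reading and not explicit text.

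**Step 2. Which exclusions can remove an exposed infant?**

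- Not intubated: the trial procedure was not completed, so this matters least.
- Failed an inclusion criterion, or met an exclusion criterion: the infant may have been intubated as allocated. These two are clearly affected.
- Consent withdrawn or retrospective consent declined: the infant may have been exposed, but consent may bar use of the data.

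**Step 3. The plan's own figure.** Section 11 assumes success in 30% of controls against 50% on nHF, at 90% power. It concludes: "two-sided alpha 0.05, at least 123 intubation episodes in each group (246 total) are required". With p̄ = 0.40:

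n = [1.960·√(2 × 0.40 × 0.60) + 1.282·√(0.30 × 0.70 + 0.50 × 0.50)]² / 0.20² ≈ 124 per group.

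Power at 123 per group is 89.8%. The stated 123 is reproduced within rounding. It supplies the arm size used below and has no other bearing on this point.

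**Step 4. Weight of one event.** 1/123 = 0.0081, or 0.8 percentage points. The SAP gives no harm rates. Assuming 1% to 5%:

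| Assumed rate | Expected events in 123 | One event as a share |
|---|---|---|
| 1% | 1.2 | 81% |
| 2% | 2.5 | 41% |
| 3% | 3.7 | 27% |
| 5% | 6.2 | 16% |

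**Step 5. Effect on a risk difference (invented counts, nHF minus control).**

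| Full counts | Removed | Result |
|---|---|---|
| 3/123 v 1/123 | none | 1.6 points |
| 3/123 v 1/123 | 3 nHF episodes with 1 event | 2/120 − 1/123 = 0.9 points |
| 3/123 v 1/123 | 5 nHF episodes with 2 events | 1/118 − 1/123 = 0.03 points |
| 3/123 v 1/123 | 3 control episodes with 1 event | 3/123 − 0/120 = 2.4 points |
| 5/123 v 2/123 | none | 2.4 points |
| 5/123 v 2/123 | 3 nHF episodes with 1 event | 4/120 − 2/123 = 1.7 points |
| 5/123 v 2/123 | 5 nHF episodes with 2 events | 3/118 − 2/123 = 0.9 points |

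One or two lost events can halve, erase or widen the contrast, depending on the arm they come from.

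**The case against.** The strongest reply is that Section 30 does not restrict harms at all. Overall principles covers every randomised episode, and the primary-outcome analysis section is where the exclusions are expressly applied. A reader who infers that the SAP states harms are compared only in the reduced set goes beyond the text. This part of the objection stands. It does not settle the matter, because Section 20 is worded as the general population and the two statements cannot both govern.

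A reader might also fault comparison by assigned arm, since the only look at treatment received concerns the primary outcome. That does not follow. Assigned arm is the randomised comparison and removes no event; the exclusions do. Treatment received is worth a listing because the per-protocol section foresees crossover.

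It may be said that the exclusion criteria were safeguarded. They were set on advice from a DSMB blinded to the arm and outcome of the episodes it discussed, and the eligibility criteria concern status that allocation cannot change. This is fair, and nothing in the SAP suggests selection by outcome. The SAP does not say who applies the criteria to each episode, or whether that person is blinded.

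Finally, the DSMB reviewed these events after 60, 125 and 180 patients, with no statement that excluded episodes were left out. That helps monitoring but does not replace the final harms table. The protocol and DSMB charter, which may hold further safety-reporting rules, are not shown.

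**Conclusion.** The point holds as a gap with a harmful default. Section 30 leaves the harms set unnamed, Overall principles and Section 20 conflict, and the more specific of the two drops events in infants who were intubated as randomised but later found ineligible. The change should be made, because following Section 20 as written can lose such events.

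The size per lost event is firm: about 0.8 percentage points of a 123-episode arm. Everything beyond that rests on assumed rates of 1% to 5% or invented counts. The three episodes put to the DSMB are not a count of losses: the SAP does not say that they were intubated, excluded or had an event.

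A reader might infer that the trial will report a safer set than it treated, or fewer harms in one arm. The document does not support that. It records no excluded episode with an event, and even if ineligible infants were at higher baseline risk, that would not push the between-arm difference in a known direction.

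**What to change.** Add to Section 30: *Harms are compared by assigned arm in all randomised episodes with an intubation attempt for which consent permits use of the data, whether or not an inclusion or exclusion criterion is later found to have been breached.*

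Add a listing of each harm by assigned arm, eligibility status and whether nHF was actually received. State in Section 20 that its exclusions define the efficacy set only, and reword Overall principles to agree.

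The cost is a few sentences and one listing. Harm denominators will differ slightly from efficacy denominators, so both should be shown. The SAP does not say whether harms were recorded to 72 hours for excluded episodes. The sponsor should confirm this and report any that were not followed.

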### 31. Statistical software

Data will be exported from the study database to STATA (StataCorp. 2019. *Stata Statistical Software: Release 16*. College Station, TX: StataCorp LLC) for analysis.

## Data Availability

The datasets during and/or analysed during the current study will be available from the corresponding author on reasonable request.
